### Timing of final analysis (14)

Results will be analysed upon database lock, following completion of all data collection stages in all sites.

### Timing of outcome assessments (15)

Outcomes will be assessed at three time points: baseline, 1 month post-intervention (4 months post-baseline), and 12 months post-intervention (16 months post-baseline).

## Statistical principles

### Confidence intervals and p values (16, 17, 18)

All reported confidence intervals will be at the 95% level. Any hypothesis testing will be undertaken at the level of statistical significance corresponding to the prespecified alpha level of *α* = 0.05 with two-tailed tests for all analyses. Minimal clinically important differences are not well understood or established for many outcomes included in this analysis. Therefore, we will not explicitly benchmark findings against these differences in any primary analyses.

### Adherence and protocol deviations (19a, b, c, d)

Protocol deviations, if they occur, are likely to relate to the rollout and availability of the intervention. All protocol deviations will be systematically recoded and detailed in the final evaluation report of the trial. Adherence will be considered as part of the process evaluation which is not covered by this SAP.

### Analysis populations (20)

The analysis populations are defined at both the family and the cluster levels. In all cases, the analysis adheres to an intention-to-treat approach. This methodology ensures analysing participants strictly according to the randomisation allocation of their cluster. At the family level, the analysis will be based on the treatment allocation of the relevant cluster and include all dyads that meet the eligibility criteria, have provided informed consent, and have valid outcome data. Data are provided by one caregiver per family. Within families, we will identify one index child, defined as the child whose birthday is coming up next. If the child is aged between 10 and 17 years at baseline, that child will be eligible for entry in the adolescent sample. In an additional round of data collection for post hoc data analyses only (around 3–5 months after intervention), we will interview all other adolescent siblings (aged 10–17 at baseline, or who have turned 10 since baseline) or co-resident adolescents in households. Analysis methods for this cohort will be treated in an addendum to this statistical analysis plan.

## Trial population

### Screening data (21)

The principal investigators (PIs) and research managers will ensure comprehensive training on the trial protocol’s inclusion and exclusion criteria for all staff members and collaborating partners. This process will uphold the trial’s screening process integrity and ensure a consistent application of participant screening across the study. The PI or designate is responsible for final decisions regarding the eligibility of participants. In instances where screening outcomes render a potential participant ineligible to be included, the rationale for this exclusion will be clearly communicated to the participant. For the participants who are deemed ineligible, all relevant data collected during the screening assessment, including any informed consent documentation and records of completed study procedures, will be retained for the lifespan of the study. Participants who meet all eligibility criteria and complete informed consent procedures will be enrolled into the trial. All screening records for eligible participants will be included in the research record for that participant and household. To facilitate the screening process, a detailed screening log will be maintained and include the following information: the screening number, participant age, date of screening, the date informed consent was obtained, and the date of study enrolment. Participants who opt not to participate in the trial will be politely asked to provide reasons for their decision to decline. In these instances, it will be explicitly communicated that they are under no obligation to disclose their reasons and may decline without reason or comment. Declining participants will not be assigned a screening number but will be captured as refusals in the data logs. All responses will be recorded as part of the screening data. The screening log should be reviewed periodically by the PI or research managers to determine if there are any trends regarding ineligibility.

### Eligibility (22)

The selection of eligible communities will focus on urban and peri-urban sub wards in Mwanza, Tanzania. These communities must meet a specific eligibility criterion, specifically having at least 30 households that are qualified participants in the national Tanzania Social Action Fund (TASAF) programme. This requirement serves as a nationally recognised indicator of poverty and vulnerability, ensuring that the communities selected are those in genuine need. However, it is important to note that only a select group of these eligible households will be part of the programme during the trial period. The study will adopt a simplified version of the TASAF eligibility criteria, as outlined in the Interagency Social Protection Assessments [16] to facilitate the selection process. In addition, the selection will also prioritise households that do not currently own a smartphone.

The trial involves three distinct participant groups. This includes caregiver, adolescents, and the staff of the implementation partner. The selection of caregivers and adolescents will be confined to eligible clusters, which include sub wards within the Mwanza Region. Sub-wards are defined as the lowest administrative structure at the community level in urban settings in Tanzania.

For caregivers from the selected sub-wards to be eligible to participate in the trial, they are required to meet several inclusion criteria. Caregivers should be 18 years or older and be the primary caregiver of an adolescent aged between 10 and 17 years old. Additionally, the caregiver should cohabit with the adolescent, sharing the same household for a minimum of four nights per week over the preceding month. Basic literacy is a criterion, assessed through a simple screening question about their reading capabilities. Suitable responses include the ability to read with slight difficulty or ease. Caregivers who report illiteracy or have significant reading challenges will be excluded. Caregivers must also consent to engage with either the ParentApp (intervention) or WASH App (control) programme and provide written or oral informed consent for full study participation.

Adolescents eligible to be included in the study are required to be aged between 10 to 17 years old at the study’s outset. They need to be dependent on a caregiver who satisfies the above specified criteria for caregivers and who have provided written or oral assent. This should be over and above obtaining the required consent from the primary caregiver for full participation in the study.

Staff members from the implementing partners will qualify for the study if they are 18 years or older, have participated in the ParentApp facilitator training workshop, and can give written or oral informed consent for participation.

The study will exclude any potential participants who exhibit severe mental health issues or acute mental disabilities if these conditions impede their capacity to provide informed consent, adhering to ethical considerations.

### Recruitment (23)

The recruitment for this pragmatic cluster-randomised trial is designed to closely mirror the processes anticipated in a government-led scale-up, thereby ensuring the real-world applicability of our findings. Recruitment will work using a collaborative effort with established partnerships with UNICEF, the Tanzanian government, and the National Institute for Medical Research (NIMR), alongside local implementation by the Investing in Children and Strengthening their Societies (ICS) organisation.

Our recruitment strategy is multifaceted, aiming to engage caregiver-adolescent dyads through a variety of channels. These include leveraging existing community groups, such as farmer’s groups, that offer natural assemblies of our target demographic. In addition to this, we will employ both traditional and digital outreach recruitment methods.

Prior to the initiation of any recruitment activities, formal approval will be secured from local community and political leaders to ensure a collaborative recruitment approach. The community leaders will be asked to take an active role in the recruitment process, ensuring comprehensive community mapping and recruitment efforts. This process ensures that the recruitment procedure is not only respectful of local community structures but is also tailored to the unique socio-cultural context of each sub ward.

Current recruitment and data collection figures are included in the CONSORT flow diagram (Fig. 1).

**Fig. 1 Fig1:**
[figure not shown]
ParentApp Randomised Controlled Trial CONSORT diagram showing current data collection figures

### Withdrawal/follow-up (24a, b, c)

Following the ethical principles guiding this trial, caregivers and adolescents have the explicit right to withdraw from the study at any point, without facing any type of repercussion or penalty. All collected data will be retained up to the point of withdrawal unless the participant requests otherwise. The study has a proactive monitoring mechanism designed to identify and address any adverse effects stemming from participation. Should it become evident that participation in the trial, or exposure to the intervention, has caused significant harm to participants or their families, the study team will take immediate action to suspend research activities. Types of harm that will be screened for include abuse, suicidality, intimate partner violence (IPV), and other forms of psychological or physical distress. Research activities will only resume if all issues can be adequately addressed, ensuring harm will not be repeated.

### Baseline patient characteristics (25a, b)

Participant recruitment and baseline assessment are undertaken on a rolling basis. Randomisation will occur once complete strata have been defined, ensuring the allocation of treatment groups is as unbiased as possible. No caregiver baseline data are used at the point of randomisation. Blocks of clusters within strata will be randomised to account for potential population differences between regions.

For each cluster, we will report on the following key characteristics:(i)District: The specific administrative district within the region of Mwanza(ii)Ward: The ward within the district, providing a finer geographical categorisation(iii)Cluster: A further breakdown within the ward to identify specific participant groups

Baseline characteristics collected from caregivers include:(i)Age(ii)Gender(iii)Relationship with adolescent(iv)Reading proficiency

Adolescents’ baseline characteristics, as reported by their caregivers, include:(i)Age(ii)Gender

## Statistical analysis

### Outcome definitions (26a, b, c)

This trial explores several outcomes, including primary and secondary, socio-demographic measures, cost-effectiveness, implementation, and exploratory. As previously noted, data collection will occur at three timepoints: baseline, 1 month post-intervention, and again at 12 months post-intervention. To ensure consistent reliability and validity across the study’s scope, the outcome measurements will be collected from both caregivers and adolescents and, unless specified otherwise, be reported independently. A consistent recall period of ‘the past 4 weeks’ will be used to optimise the precision of potential behaviour change detection attributable to the intervention. All outcomes are supported by an established theoretical framework, with intervention effects rigorously evaluated through empirical analysis. Tools will be back translated into Kiswahili and undergo extensive local review to ensure language accuracy and cultural relevance; certain measures have been adapted following feedback from the pilot phase of the trial with the aim of enhancing comprehensibility and contextual relevance.

#### Primary outcomes

Primary outcomes for both caregivers and adolescents include child maltreatment, sexual violence victimisation, and sexual violence vulnerability. *Child maltreatment* includes both physical [1a] and emotional [1b] abuse and will be assessed using subscales of the Caregiver and Child Versions of the International Society for the Prevention of Child Abuse and Neglect Screen Tool for Trials (ICAST-Trials) [17].

*Sexual violence victimisation [3a; 3b; 3c; 3h]* will combine measures and items of contact sexual abuse, non-contact sexual abuse, alcohol-facilitated forced sex, and transactional sex; these measures are from adolescent reports only. *Sexual violence vulnerability [3e]*, both adolescent and caregiver reported*,* will combine items of exposure to high-risk situations for sexual violence. These two outcomes will be evaluated using a combination of items from the ICAST-Trial measures [17], the CDC Violence Against Children and Youth Surveys [18], and a locally derived sexual violence vulnerability scale developed through consultation with families and practitioners. This approach differs slightly from what was reported in the study protocol, in that these two outcomes will then be combined to form a single primary outcome of *sexual violence victimisation and vulnerability [3a; 3b; 3c; 3h; 3e]*. To address the intricate dynamics of sexual violence victimisation and vulnerability, additional exploratory analysis will disaggregate outcomes by gender.

#### Secondary outcomes

The secondary outcomes are presented in Table 2.

#### Exploratory outcomes

*Use of internet and exposure to online violence risk*—the Global Partnership to End Violence Against Children’s Disrupting Harm project [19] (adapted)*Digital literacy*—questions developed by the research team to assess digital skills*Adolescent externalising and internalising problem behaviour*—the Child and Adolescent Behavior Inventory (CABI) [20]. Items are caregiver reported only*Adolescent internalising mental health distress, depression and anxiety – PHQ (adolescent only)**Substance use*—the WHO Alcohol Use Disorders Identification Test [21] and the WHO Global School-based Health Survey [22] (adapted)*Engaged responsive parenting* encompassing cross-cultural indicators of playful learning [23], characteristics of learning through play [24, 25] and positive parenting—the APQ positive parenting and involvement subscales, the parent-child communication scale, and parent support for school. Caregiver’s engagement with playful activities in the app (e.g. number of playful activities completed) will be measured through app engagement data

#### Socio-demographic measures

Baseline socio-demographics for both caregiver and adolescent will include items from the Multiple Indicator Cluster Surveys (MICS) [26] as well as general questions:AgeGenderAssessment of disability (baseline and 1 month follow-up)Assessment of basic literacyHousehold structureAdolescent’s relationship to the caregiverHousehold employmentSchool enrolmentRelationship statusOrphanhoodAccess to social protection (e.g. government cash transfers)

#### Cost-effectiveness outcomes

Implementation costs will be calculated through weekly surveys completed by facilitators, recording time and data spent in WhatsApp group live chats, additional remote support, any preparatory efforts from facilitators, and basic participant engagement statistics. This will enable accurate and real-time data to inform implementation costs. Delivery costs will be retrospectively calculated, including facilitator training and support, mobile device provision, programme onboarding, and app maintenance. For cost-effectiveness measurements, a visual analogue 0–100 scale will be used to inform quality-adjusted life years (QALY) in the pre and post surveys for both adolescents and caregivers. To better estimate cost and savings of the intervention across multiple outcomes and VAC pathways, we will deploy a multi-outcome discounted cost-effectiveness approach [27, 28].

#### Implementation outcomes

Implementation outcomes will be assessed to understand intervention fidelity, uptake, and retention. Data on the amount, frequency, and duration of app usage, as well as the nature, scope, and depth of content engagement, will be collected through app-generated statistics. Weekly facilitator surveys, as described under cost-effectiveness outcomes, will be used to collect facilitator-reported experiences such as implementation challenges, successes, and other relevant insights. To explore the quality of support, a random sampling of the moderated WhatsApp live chat sessions will be assessed; the team will ensure complete transparency in any monitoring activities and participant confidentiality will be maintained. Interviews with select implementing staff will provide supplementary qualitative insights.

Implementation outcomes will further include exploration of intervention acceptability, benefits, and challenges through qualitative interviews with caregivers, adolescents, and implementing staff. Open-ended questions on ParentApp acceptability, cultural relevance, delivery experiences, usage satisfaction and engagement, and perceived benefits and challenges will be explored. Focus group discussions with implementing staff will be explore facilitator experiences of intervention delivery, processes, barriers, and recommendations for future implementation.

#### Exploratory interviews with siblings

With a small amount of additional funding, exploratory data collection will take place with adolescent siblings or co-residents in participating households. The survey tool will align with the 1 month follow-up survey administered to trial caregiver-adolescent dyads, with minor alterations. This additional exploratory outcome will allow us to ascertain potential spill-over effects of the intervention to other children within the household.

### Analysis methods (27a, b, c, d, e)

#### Analysis methods for primary and secondary outcomes

The primary method of analysis will be generalised linear mixed-effects models to account for the hierarchical nature of the data. This will involve specifying a three-level model with adjustment for person-level characteristics and multiple imputation. In this three-level model, measurement waves are nested within a person, and this is nested within a sub-ward (i.e. cluster). Each regression will delineate the relationships at each level where necessary. At the cluster level (level 3), the model incorporates terms for randomisation stratification variables and contextual covariates such as the percentage of male caregivers within each cluster. At variance with the protocol, a term for intervention allocation will not be included due to the repeated measures nature of the analysis (and the subsequent uninterpretability of a ‘baseline’ intervention term). This is equivalent to constraining the intercepts to be equal by arm. At the individual level (level 2), the model adjusts for demographic characteristics centred at the overall sample mean. For caregiver report models, this includes caregiver age, caregiver gender, caregiver-adolescent relationship, caregiver disability, child age, child gender, and child disability; caregiver gender specifically is centred at the overall cluster mean to facilitate interpretable comparisons. For child report models, this includes caregiver-adolescent relationship, child age, child gender, and child disability. At level 1, the model includes a categorical time variable and interactions between intervention allocation and time (i.e. the test of intervention effectiveness). If an event occurs whereby more than participant (adolescent or caregiver) is recruited from a single household, we will implement a clustered standard error structure on level 2. If a three-level model fails to converge, we will use a two-level model with measurement waves within person, clustering standard errors by sub-ward.

The regression link functions will be tailored based on the distributional characteristic of each outcome measure. For example, a logit link will be used when outcome measures are binary and a Poisson link for outcome measures with count data which include integer values from 0.

The intervention’s effectiveness will be evaluated through multiparameter Wald tests or likelihood ratio tests as appropriate, comparing models with and without intervention-by-time interactions to assess the totality of the intervention’s impact. Furthermore, the use of Wald tests will assess the significance of specific fixed effects model coefficients, particularly in relation to the intervention-by-time interactions. In addition to the primary analysis, we will conduct both adjusted analyses with unimputed data and unadjusted analyses with unimputed data, which include terms for stratification, time, and intervention-by-time, to provide a baseline estimate of intervention effectiveness without covariate adjustments.

Both Wald tests and marginal effects plots will be used to evaluate differences of outcome interactions by intervention group and will be supported by the computation of intra-cluster correlation coefficient (ICC) for hierarchical data. Depending on the distribution of the data, i.e. binary or Poisson, median incidence rate ratios (IRR) or odds ratios for hierarchical and non-normally distributed data will be respectively calculated.

The *p*-value threshold will be 0.05 for all pre-specified analyses. However, due to multiple comparisons planned for exploratory analyses, a sharpened *q*-value will be used with respect to all exploratory analyses to adjust the *p*-value threshold for statistical significance to reduce the likelihood of false positives.

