## Study methods

### Trial design (9)

The design of this study is a pragmatic, two-arm, cluster-randomised controlled trial (RCT) within the urban and peri-urban settings of Mwanza, Tanzania. The study’s assessments will be collected at baseline, followed by evaluations at 1 month post intervention and at 12 months post intervention. The trial encompasses the randomisation of 80 urban and peri-urban clusters, each consisting of approximately 30 caregiver-adolescent dyads. Randomisation will follow a structured design and be conducted at the cluster level, adhering to a strict 1:1 allocation ratio.

Caregivers in both the intervention arm and control arm will be provided with an entry level, locally sold, smartphone; phones will be preloaded with the Kiswahili version of ParentApp for the intervention arm and a simple hygiene programme, WASH App, for the control arm. The intervention group will also be added to facilitated WhatsApp groups for the exchange of insights and learnings among caregivers.

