### Sample size (11)

The sample size is based on a detailed power calculation informed by preliminary pilot study data, using generalised Poisson linear mixed-effect models. These calculations posit that, to achieve a statistical power of 80% against an anticipated effect size of 0.95 and a control group mean outcome of 4, while accounting for potential attrition rates within both the control and intervention arms, a minimum ensemble of 80 clusters, each comprising 30 dyads, is required. The trial will therefore enrol a cohort of approximately 2400 caregiver-adolescent dyads or 4800 participants.

A subset of participants, comprising 40 to 60 caregivers and 20 to 30 adolescents, will be invited to engage in post-intervention qualitative interviews. These discussions are aimed at eliciting in-depth insights into the experiential dimensions of the programme, thereby enriching the quantitative data. Additionally, semi-structured interviews will be conducted with a representative sample of 10 implementing staff members, offering a comprehensive perspective on programme delivery dynamics.

Expanding the impact of the study, we intend to include adolescent siblings or co-resident adolescents present within approximately 50% of the participating households (estimated *n* = 2610) in the post-intervention assessment phase. This strategic inclusion aims to ascertain the broader familial impact of the intervention, thereby capturing any auxiliary effects on the household’s adolescent population not directly involved in the primary intervention activities.

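### The primary three-level model names no sub-ward-by-wave variation, so the standard error of the allocation-by-time effect is too small if sub-wards change differently over time

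*Protocol article*

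**What the plan says.** The section Analysis methods for primary and secondary outcomes sets the primary model out level by level: "In this three-level model, measurement waves are nested within a person, and this is nested within a sub-ward (i.e. cluster". The sub-ward level carries the stratification variables and contextual covariates, and the person level carries demographics. The wave level carries categorical time and the allocation-by-time interactions, which the section identifies as the test of effectiveness. There is no allocation main effect, so the arms share one baseline mean.

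The random effects are not listed. No sub-ward-by-wave effect or random time slope is named.

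Clustered standard errors appear twice in that section. If more than one participant comes from a household, "we will implement a clustered standard error structure on level 2". If the three-level model does not converge, a two-level model is fitted, "clustering standard errors by sub-ward".

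Under Sample size (11), "a minimum ensemble of 80 clusters, each comprising 30 dyads, is required". No ICC or variance component is given there.

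**The concern.** Sub-wards are randomised, so the effect should be judged against how much sub-wards in the same arm differ in their change over time. One sub-ward intercept shared by all three waves largely cancels from a change over time. If a sub-ward shifts as a whole between waves, a model with only person and sub-ward intercepts puts that shift into the individual residual and averages it over about 30 people, although it is common to all of them.

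The article gives reasons to expect some variation of this kind. Recruitment and baseline were rolling, by cluster, between April and September 2023. The 1-month follow-up had run from August 2023 to at least March 2024, and the 12-month follow-up is planned for September 2024 to April 2025. Recall covers four weeks. Sub-wards can therefore be measured in different calendar periods within one nominal wave, up to 16 months after baseline.

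At stake is the 0.05 level of the primary and secondary tests. There is also an asymmetry: an outcome whose three-level model fails to converge would get errors robust to this variation, and one that converges would not.

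**Working it through.** **The plan's own figures.** 80 × 30 = 2400 dyads and 2400 × 2 = 4800 participants, as stated ("approximately 2400 caregiver-adolescent dyads or 4800 participants"). The 80% power cannot be reproduced, because the variance components, the attrition rate and the scale of the effect size are not given. The present point does not dispute it.

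**Inputs from the article.** 80 sub-wards at 1:1, so 40 per arm; 30 people per sub-ward for one informant; three waves; arms equal at baseline; two-sided α = 0.05.

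**Assumed inputs.** Total variance 1. The ICC is the sub-ward share of that variance. A share s of the sub-ward variance is specific to a wave. The remaining variance, 1 − ICC, is split equally between person and residual (person correlation 0.5).

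**Method.** The working model has person and sub-ward intercepts only, with variances at their maximum-likelihood limit when the truth also contains sub-ward-by-wave variance. Its model-based SE for the 12-month interaction is compared with the sandwich (true) SE. Single-test type I error = 2Φ(−1.96 × model SE / true SE).

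**Hand check at ICC 0.05, s = 0.20.**
- Wave-specific sub-ward variance: 0.05 × 0.20 = 0.010. Residual variance: 0.95 × 0.5 = 0.475.
- The working model absorbs the 0.010 into the residual: 0.475 + 0.010 = 0.485.
- It therefore gives a sub-ward mean a wave-level variance of 0.485 / 30 = 0.0162.
- The true value is 0.010 + 0.475 / 30 = 0.0258.
- SE ratio for a plain change contrast: √(0.0162 / 0.0258) = 0.79. The full calculation with the common baseline gives 0.0380 / 0.0471 = 0.81.
- Type I error: 2Φ(−1.96 × 0.807) = 11.4%.

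**Results (12-month interaction).**

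| ICC | Wave-specific share | Model SE | True SE | Ratio | Type I, single | Type I, joint 2-df |
|---|---|---|---|---|---|---|
| 0.05 | 0 | 0.0378 | 0.0378 | 1.00 | 5.0% | 5.0% |
| 0.01 | 10% | 0.0365 | 0.0373 | 0.98 | 5.6% | 5.8% |
| 0.02 | 10% | 0.0371 | 0.0389 | 0.95 | 6.2% | 6.7% |
| 0.02 | 20% | 0.0371 | 0.0406 | 0.91 | 7.3% | 8.4% |
| 0.05 | 10% | 0.0379 | 0.0428 | 0.89 | 8.2% | 9.6% |
| 0.05 | 20% | 0.0380 | 0.0471 | 0.81 | 11.4% | 14.5% |
| 0.10 | 20% | 0.0382 | 0.0561 | 0.68 | 18% | 25% |

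**Count-outcome check.** Poisson linearised on the log scale, with residual 1/4 at the article's control mean of 4, an assumed person variance of 0.5 and a 20% wave-specific share:
- Sub-ward SD 0.1: SE 0.0270 against 0.0297, type I error 7.5% (joint 8.5%).
- Sub-ward SD 0.2: SE 0.0278 against 0.0383, type I error 15.4% (joint 20.7%).

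**After the fix.** At ICC 0.05 and a 20% share, adding the sub-ward-by-wave intercept gives a correct SE of 0.0466.

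**The case against.** The strongest reply is that the article never lists its random effects. The cited sentence gives the nesting of levels, the text after it lists fixed terms, and the section says relationships at each level will be specified where needed. A sub-ward-by-wave term is compatible with that and is not excluded. This stands. A reader might infer that the model certainly has only two intercepts, but the article does not say so. It is the natural reading, because the section goes through the model level by level, puts the test at the wave level and reserves sub-ward-clustered errors for the fallback.

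A reader might also infer that type I error is inflated for every outcome. That is not supported. Without wave-specific variance the error is 5%, with small inputs the excess is under one percentage point, and the article gives neither the ICC nor the share. The Gaussian figures are also only a proxy for count and binary outcomes.

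Two further readings should not be used to strengthen the point:
- **Extra clustering in the intervention arm.** Under Trial design (9), "The intervention group will also be added to facilitated WhatsApp groups for the exchange of insights and learnings among caregivers". The article does not say these groups are formed within sub-wards, and no one-arm clustering has been quantified here.
- **The level-2 clustering rule ignores sub-ward dependence.** It is a contingency for several participants from one household, inside a model that keeps the sub-ward level. Analysis populations (20) takes one caregiver and one index child per family, so it should be rare.

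Finally, the fallback has a coherent reason to cluster by sub-ward, since it drops that level. This explains the asymmetry but does not protect the three-level model.

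**Conclusion.** The point holds in conditional form. As described, the primary model names no sub-ward-by-wave variation, although the tested effect is a change over time between arms randomised by sub-ward. On the natural reading its standard error is right only if sub-wards within an arm change alike. The article does not justify that assumption, and its rolling calendar makes exact equality unlikely.

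The consequence runs from negligible to serious over inputs that are all assumed. That uncertainty, and the unlisted random effects, make this a should-fix and not a must-fix. The mechanism itself does not depend on the assumed values, and the remedy is cheap.

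**What to change.** - State the random effects of the primary model.
- Either add a sub-ward-by-wave random intercept (one variance, estimated from 80 × 3 = 240 sub-ward-waves), or report sub-ward-clustered robust standard errors for every primary and secondary outcome, whether or not the three-level model converges.
- If robust errors are chosen, use the Wald version of the joint test. The likelihood ratio test, which the plan also allows, would not carry the correction.
- Where several participants come from one household, cluster at the sub-ward, which contains households.

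The cost is a few lines of wording and one extra random term or variance option. 80 clusters are enough for robust errors, and the plan already accepts them in its fallback. An extra random term may make convergence harder for sparse outcomes; the robust option avoids this. Confidence intervals widen where sub-wards drift apart: by about 2% at ICC 0.01 with a 10% share (0.0373 / 0.0365) and about 23% at ICC 0.05 with a 20% share (0.0466 / 0.0380). With no drift they are essentially unchanged.
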